###### Internalized AIDS stigma

We will use the seven-item internalized AIDS-related stigma scale for people infected with HIV. Items reflect self-defacing beliefs and negative perceptions of people living with HIV/AIDS^32^. In previous studies with the same scale, a Cronback a reliability coefficient of 0.72-0.76 was found^33^. This questionnaire will be taken at baseline and every follow up visit.

#### Alcohol consumption (annex 3)

The 10-item Alcohol Disorder Identification Test (AUDIT)^34^ assesses alcohol consumption level (3 items), symptoms of alcohol dependence (3 items), and problems associated with alcohol use (4 items). Responses to items on the AUDIT are rated on a 4-point Likert scale from 0 to 4, with a maximum score of 40 points. AUDIT scores higher than 19 indicate more severe levels of risk; scores of 8-19 in men and 7-19 in women indicate a tendency to problematic drinking.

To reduce the stigma of alcohol use, WHO suggests to integrate the screening of alcohol use with screening of other health related behaviors. For this reason two questions will be asked about the use of tobacco products and anthropometric measurements will be taken to assess the riskfactor of overweight (height, weight, waist- and hip circumference)

This questionnaire will be administered at baseline, 3 and 12 months follow-up visits. All questionnaires will be administered in English or Tswana, the two languages predominantly spoken by nearly all clinic patients.

#### HIV related information Data Extract Sheet (Annex 4)

A researcher designed patient information extract sheet will be used to record information related to the HIV infection and will include questions about date of first positive HIV test, start date ART, ART regimen and co-infections. The patientfile will be used to obtain additional information. The computerized laboratory data system will be used to obtain the laboratory results. At follow up CD4 cell counts and viral load will be obtained from the computerized laboratory data system. This data extract sheet will be taken at baseline and laboratory and clinical information will be collected at every study visit; at baseline, 3 and 12 months.

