#### Objectives:

- - 1. To measure the prevalence of alcohol consumption among HIV positive hospital outpatients;
    2. To describe drinking patterns, health status, quality of life and sexual behavior among HIV positive out-patients, and identify medium risk drinkers needing intervention;
    3. To compare level of alcohol consumption, health status, quality of life, level of adherence to ART and sexual behavior among medium risk drinkers within the previously identified group between pre intervention, 3 months and 12 months after intervention;
    4. To compare **levels of** (a) alcohol consumption, (b) adherence level to ART, (c) quality of life, (d) health status and (e) number of patients with virological and immunological failure, between intervention and control group at 3 and 12 months;
    5. To compare **changes in** (a) alcohol consumption, (b) adherence level to ART, (c) quality of life, (d) health status and (e) number of patients with virological and immunological failure, between intervention and control group at 3 and 12 months.

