# Data Analysis

*Definition of virological failure:*

We follow the definition used in the national guidelines in which virological failure is defined as a repeat VL ≥ 1000 copies/ml after intense adherence assessment^38^.

*Definition of immunological failure:*

Immunological failure is defined according to the WHO definition. Failure is defined as a fall of CD4 count to pretherapy baseline (or below), *or* a 50% fall from the on-treatment peak value (if known) *or* a persistent CD4 levels below 100 cells/mm^3^.^39^

Means, standard deviations, and percentages will be used for descriptive statistics. T-test for continuous data and chi-square for categorical data will be used to examine differences between groups. Generalized Linear Model Repeated Measures 2 x 3 Analysis of Variance (ANOVA) will be used for comparing observations (alcohol use score) across the three contact periods to demonstrate a treatment intervention x time interaction.Observations with a single follow-up point missing (at either 3 and 12 months) will be imputed with the available follow-up. Data for participants who are lost to follow-up at 3 and 12 months will be imputed using baseline values. SPSS for Windows version 18.0 (SPSS, Inc., Chicago, IL) will be used for calculations.

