#### Confidentiality

All research data obtained from participants will be labeled with a code number and not the participant’s name. Only the code number will appear on measures, data records, and computer files.

Obtaining Consent

Consent to participate will be obtained in a 2-stage process. Research assistants will initially ask for informed consent to conduct health screening and collect some basic demographic information and check eligibility to take part. No identifiable information will be collected at this stage. Patients who then are positive on the AUDIT (alcohol medium risk score), as applicable, will have the study explained to them verbally by another research assistant counselor and in writing (using the patient information sheet, annex 7-8). Informed consent will be obtained at this second stage which will include permission to give the patient's data and contact details to the research staff, and participate in the intervention and follow up after 3 and 12 months (see Annex 7-8: Consent form).

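### CD4 and viral-load collection is worded by study visit, and the fill-in rules exempt no outcome, so failure status could be filled in where a real laboratory result exists

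*Protocol*

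**What the plan says.** Objectives 4(e) and 5(e) compare levels of, and changes in, the "number of patients with virological and immunological failure, between intervention and control group at 3 and 12 months".

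Under HIV related information Data Extract Sheet (Annex 4), the source of the results is a record, not the participant: "At follow up CD4 cell counts and viral load will be obtained from the computerized laboratory data system". The same paragraph sets the timing by visit: "laboratory and clinical information will be collected at every study visit; at baseline, 3 and 12 months". The Annex 4 form is addressed to the interviewer and asks for the most recent readings in the medical file.

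Data Analysis gives two fill-in rules. For one missed follow-up: "Observations with a single follow-up point missing (at either 3 and 12 months) will be imputed with the available follow-up". For both missed: "Data for participants who are lost to follow-up at 3 and 12 months will be imputed using baseline values". Neither rule names the outcomes that it covers or excludes.

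Procedure answers drop-out with at least six attempts to contact the patient. It does not mention looking up the records of someone who cannot be reached. The second-stage consent includes "permission to give the patient's data and contact details to the research staff".

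**The concern.** Interview outcomes such as the AUDIT score are lost when a participant does not come. Laboratory outcomes need not be, because the source can be consulted without the participant. If extraction happens only when a visit takes place, and the fill-in rules then apply to all data, a participant who avoids interviews but remains in routine HIV care is analysed with a substitute although a real result may be on the system.

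The substitutes suit failure status badly. A baseline value makes the change under objective 5(e) zero by construction. The rule for one missed follow-up can let a 3-month result stand for month 12. The definition "virological failure is defined as a repeat VL ≥ 1000 copies/ml after intense adherence assessment" rests on more than one measurement over time, which a single carried value cannot supply.

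Those who stop attending may plausibly have poorer adherence, so their failures are the ones most easily missed. If loss also differs by arm, the comparison between arms is distorted, not only the level within each arm.

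**Working it through.** **1. How many participants could be affected**

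Sample size calculation gives 251 per group, a 10% drop-out allowance and 276 per group (552 in total). The 251 reproduces closely. Odds of 9 (90% adherence) × 0.480 = 4.32, and 4.32 / 5.32 = 81.2%. The pooled two-proportion formula for 90% v 81.2%, with 80% power and two-sided 5%, gives 249. Then 251 × 1.10 = 276.1, matching 276.

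- Per arm: 0.10 × 276 = 27.6, about 28.
- Both arms: 0.10 × 552 = 55.2, about 55.

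This is an upper figure at the planned loss. It shrinks for those who left care or had no test near the time point. The protocol gives no share for either group.

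**2. What the baseline rule does, read literally**

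Let L be the share of an arm missing both follow-ups, f their true failure proportion at 12 months and b their failure proportion at baseline.

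- Recorded minus true proportion in one arm = L × (b − f).
- Distortion of the arm difference (intervention minus control) = L_I × (b − f_I) − L_C × (b − f_C).

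If L and f are the same in both arms, with common b, the second expression is zero. Each level is off, but the comparison is not.

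**3. Illustrations**

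The protocol gives no failure rates and no loss by arm, so every rate here is an assumption, apart from the 10% overall loss.

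Example A: failure 10% among attenders in both arms, 30% among the lost, 5% at baseline.

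| Loss (control / intervention) | True (control v intervention) | Recorded |
| --- | --- | --- |
| 10% / 10% | 12.0% v 12.0% | 9.5% v 9.5% |
| 15% / 5% | 13.0% v 11.0% | 9.25% v 9.75% |

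- Equal loss: 0.90 × 0.10 + 0.10 × 0.30 = 0.120 true; 0.90 × 0.10 + 0.10 × 0.05 = 0.095 recorded.
- Control at 15%: 0.85 × 0.10 + 0.15 × 0.30 = 0.130 true; 0.85 × 0.10 + 0.15 × 0.05 = 0.0925 recorded.
- Intervention at 5%: 0.95 × 0.10 + 0.05 × 0.30 = 0.110 true; 0.95 × 0.10 + 0.05 × 0.05 = 0.0975 recorded.

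With unequal loss, a 2.0-point advantage for the intervention is recorded as 0.5 points the other way. With equal loss, both arms are understated by 2.5 points and the difference stays at zero.

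Example B: baseline failure 10 to 20%, attenders unchanged from baseline in both arms, failure 30 to 50% among the lost.

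- At 10% loss each arm is understated by 0.10 × (0.30 − 0.20) = 1 point up to 0.10 × (0.50 − 0.10) = 4 points.
- At 15% v 5% loss the true difference is (0.15 − 0.05) × 0.10 = 1 point up to (0.15 − 0.05) × 0.40 = 4 points, and it is recorded as zero.

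**4. What extraction could recover**

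In Example A with 15% v 5% loss, if every lost participant has a retrievable result, the true 13.0% v 11.0% is obtained. If none has, and absent results are left out as missing, only attenders remain and the figure is 10% v 10%. The gain depends on how many stay in care and are tested.

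**The case against.** The strongest reply is that the protocol may already do what is wanted. The visit wording can be read as a schedule of time points. Annex 4 is a chart-extraction form, and no sentence makes extraction conditional on attendance. A result taken from the system is not missing, so nothing is filled in. This reading is possible. Against it, the form is addressed to the interviewer, and the stated response to drop-out is contact attempts only.

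Second, the fill-in sentences follow directly on the repeated-measures ANOVA, which "will be used for comparing observations (alcohol use score) across the three contact periods", and may be meant for that score alone. That too is possible. But the second sentence speaks of participants' data without limit, so the literal reading covers laboratory outcomes.

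Third, a reader might infer that the laboratory system holds the true results of those who drop out. The documents do not say so. Procedure describes 3 and 12 months as ordinary HIV-care visit intervals. That makes results plausible for patients still in care, but it also suggests that many who miss both points have left care.

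Fourth, consent. The forms are not available here, and Adequacy of Protection against Risks lets participants stop data collection at any time. Whether extraction may continue after that cannot be settled from the text.

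These replies narrow the point. They do not remove it, because the text as it stands permits the literal reading.

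**Conclusion.** The wording should be tightened in two places. Collection of laboratory outcomes is phrased by visit although the source does not need one, and the fill-in rules exempt nothing. Followed literally, failure status is filled in for participants who miss interviews but stay in care, even where a real result exists. That understates change and can bias the arm comparison if loss, or failure among the lost, differs by arm.

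The size is unknown. Up to about 28 per arm could be affected at the planned 10% loss, and fewer in practice for the reasons above. Baseline values apply only to those who miss both follow-ups; those who miss one get the other follow-up value.

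A reader might conclude that the comparison will be biased or even reversed. The documents do not support that. The reversal needs assumed loss of 15% v 5% and assumed failure rates, while the protocol plans 10% overall. With equal loss and equal failure rates there is no between-arm bias. Failure is also one of five outcomes in objectives 4 and 5: the sample size rests on adherence and the ANOVA on the alcohol score.

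**What to change.** In the Data Extract Sheet section, state that CD4, viral load and regimen are extracted from the laboratory system and patient file at 3 and 12 months for every randomised participant, whether or not the interview took place, unless permission to use records is withdrawn or the consent does not cover it. Record withdrawal from interviews separately from withdrawal of permission to use records, and check that the consent form allows the distinction.

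In Data Analysis, state that neither the baseline rule nor the other-follow-up rule applies to laboratory outcomes: the extracted result is used, and where none exists the outcome is treated as missing.

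The cost is about 55 extra record look-ups per time point (10% of 552) and one item on the withdrawal record, with no extra patient contact. Participants who left care will still lack results, so some missing data will remain.

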#### Assessment of adherence to ART (Annex 5)

###### Visual Analog Scale (VAS)

The 30-day visual analog scale (VAS) provides an overall adherence assessment for a one-month period. The VAS has been validated in resource-limited settings^35,36^. Adherence levels assessed from the VAS are defined as follows: full adherence=100%, partial adherence: between ≥95% and <100%; and non-adherence as <95% of prescribed doses taken in the past 30 days. The VAS will be assessed at baseline for patients who are already on ART and on any follow up visit if the patient is on ART.

###### Data from pharmacy:

###### Pill count

Unannounced home based pill counts are a reliable means to estimate adherence, but are limited by costs and logistical feasibility. Kalichman et al. ^37^ ^[[1]](#endnote-1)^ showed that a high degree of concordance was observed between phone- and home-based number of pills counted (Intraclass Correlation, ICC=0.997, 95% CI 0.995-0.998, P<0.001). The concordance between pill counts was not influences by participants’ educations or health literacy. The adherence determined by telephone-based pill counts also corresponded with patient viral load, providing evidence for criterion-related validity.

Practical: The patient is called by phone by research assistant and asked to put all the pills on flat surface. The patient is asked to read the medication label and to count the pills. This is repeated for all the medication. The telephonic pill counts will be repeated at baseline at all follow up assessments. Since the pill count is unannounced, it can take place up to 2 months after the patient has been seen by the research nurse for assessment.

To compare the number of pills that were dispensed and that are remaining at the pill count. The following formula gives the % adherence:

| Did the client return the medication containers?  NO  YES  $\% Adherence= \frac{Dispensed-Returned}{Expected to be taken} X 100$ |
| --- |

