#### Procedure

The procedure follows the procedure of the main protocol.

Universal screening of all presenting HIV out-patients will be done. All consecutive HIV positive clients visiting the out-patient department will be screened for alcohol problems and randomized into an intervention or control group. Randomization will be done by a remote computer to generate numbers for intervention and control. Research assistant 1 will ask for consent from patients attending the hospital out-patient department to participate in the study, i.e. do a baseline assessment using the AUDIT questionnaire. Research assistant 1 will not be involved in delivering treatment. Research assistant 2 will score the results of the alcohol test section of the questionnaire. Clinic out-patients who score 8-19 for men and 7-19 for women on the AUDIT questionnaire after screening (risky drinkers) will be included in this study. Patients with a score of 20 and above on the AUDIT (with probable alcohol dependence) will be referred for further management. Additional information of the patients will be collected using the data collection instruments. Research assistant 2 will then check the random numbers which allocate the case to the intervention arm or control arms. Research assistant 2 will carry out the intervention for all the participants, after which they will be followed up at 3 and 12 months (which are standard visit intervals for the follow up of the HIV care), and assessments will be done by Research assistant 1, who will be blinded to the intervention allocation of the participants. In the event of a drop-out, at least six individual attempts will be made to contact patients by telephone and letter. Even if a contact was not successful at either follow up point, further attempts will be made at any next follow up point. Sampling will occur throughout all hours of clinic operation over a 3-month period. Two-hundred and seventy six patients will be recruited from hospital out-patient departments. Patients will be offered a drink (soda, water) during the interviews.

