# Interventions

#### Experimental arm:

###### Brief intervention

Participants who are randomized in the intervention arm receive personalized feedback on their AUDIT results, a health education leaflet (Annex 6), plus brief counselling about reducing excessive drinking, during a one session 20 minute intervention.

The steps of brief counselling are: 1) Identify any alcohol related problems mentioned in the interview, 2) Introduce the sensible drinking leaflet, and emphasise the idea of sensible limits, and make sure that patients realize that they are in the medium-risk drinking category, 3) Work through the first 3 sections of the problem solving manual while mentioning the value of reviewing the other sections, 4) Describe drinking diary cards 5) Identify a helper, and 6) mention the 3, 6 and 12 months follow-up. The brief intervention will be based on the WHO brief intervention package for hazardous and harmful drinking^36^. The Information-Motivation-Behavioural Skills (IMB) Model

will be used to guide the alcohol reduction intervention in South Africa.

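### The baseline telephone pill count may be made after allocation and counselling, so change in pill-count adherence can lose part of any treatment effect

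*Protocol*

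**What the plan says.** On scheduling, the Protocol's Pill count section states: "The telephonic pill counts will be repeated at baseline at all follow up assessments". On timing it adds: "Since the pill count is unannounced, it can take place up to 2 months after the patient has been seen by the research nurse". The adherence formula there divides pills dispensed minus pills returned by pills expected to be taken. It sets no look-back period.

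The Procedure section gives an order of events. The AUDIT is scored and further data are collected with the study instruments. Next, "Research assistant 2 will then check the random numbers which allocate the case to the intervention arm or control arms". Then, "Research assistant 2 will carry out the intervention for all the participants, after which they will be followed up at 3 and 12 months". Under Brief intervention, the whole exposure is delivered "during a one session 20 minute intervention".

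Two parts of the plan use a baseline adherence value. Objective 5 compares between arms the "changes in (a) alcohol consumption, (b) adherence level to ART", at 3 and 12 months. The Data Analysis section says: "Data for participants who are lost to follow-up at 3 and 12 months will be imputed using baseline values". That rule is not limited to any one outcome.

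Adherence is also measured by a 30-day VAS, taken at baseline in patients already on ART. The 2-month allowance is not stated for the VAS.

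**The concern.** A change score needs a starting value that treatment cannot have touched. Here the starting count may come up to two months after a session that delivers the full intervention at once. If counselling has by then altered adherence, that alteration sits in the value being subtracted, and the arms look more alike on change than they are. A post-randomisation value is also unsuitable as an adjustment covariate. Used under the imputation rule, it would enter an early follow-up value as if it were a pre-treatment one.

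This is a matter of when data are collected. If no count is made before allocation, no later analysis can supply one. Adherence is the outcome on which the sample size rests, and the pill count is the only adherence measure in the protocol besides self-report.

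**Working it through.** **1. The plan's own figure.** Sample size calculation: 90% adherence, odds ratio 0.480, 80% power, two-sided 5%.

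- Odds at 90% = 9; 9 × 0.48 = 4.32; 4.32/5.32 = 0.812. The difference is 0.900 − 0.812 = 0.088, or 8.8 points.
- Mean proportion = 0.856. n = (1.960 + 0.842)² × 2 × 0.856 × 0.144 / 0.088² ≈ 250.02 with unrounded inputs, rounded up to 251 per group. The Fleiss formula without continuity correction gives 249.

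The stated 251 is reproduced and is not in dispute. It rests on a comparison of levels. The 8.8 points serve below only as a yardstick.

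**2. Order of events.**

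| Step | Source | Timing |
|---|---|---|
| AUDIT and other baseline data | Procedure | before allocation |
| Random numbers checked | Procedure | next |
| Single 20-minute session | Procedure; Brief intervention | after allocation |
| Baseline telephone count | Pill count | up to 2 months after the assessment |
| Follow-up | Procedure | 3 and 12 months |

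Nothing in the Pill count section requires the first call to precede allocation. That the session takes place at the same visit is implied by this order, not stated.

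**3. Effect on the change comparison.** Let Δ be the arm difference at follow-up and f the share of it already present at the first count. The expected arm difference in change is Δ − fΔ = (1 − f)Δ. With Δ = 8.8 points:

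| f | 0 | 0.25 | 0.5 | 0.75 | 1 |
|---|---|---|---|---|---|
| Points left | 8.8 | 6.6 | 4.4 | 2.2 | 0 |

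**4. How large might f be?** The documents do not say. The cases below are assumptions. The first three take the session to be at the baseline visit, with a prompt and constant effect, so that f equals the share of the count window falling after the session.

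- *Calls uniform over days 0–60, 30-day look-back.* The mean of min(t/30, 1) is 0.5 × 0.5 + 0.5 × 1 = 0.75, leaving 2.2 points.
- *Same calls, 30-day refills at random phase.* Calls on days 30–60 have share 1. Calls on days 0–30 average ∫₀¹(u − u ln u)du = 1/2 + 1/4 = 0.75. Overall 0.5 × 0.75 + 0.5 × 1 = 0.875, leaving 1.1 points.
- *Pills dispensed on the visit day.* The whole window follows the session: f = 1, leaving 0.
- *Effect building in a straight line over 12 months, counts treated as point measurements and follow-up counts on their due dates.* A call at the 2-month limit gives f = 2/12 = 0.17 against month 12 and 2/3 = 0.67 against month 3. A call at 1 month gives 0.08 and 0.33.
- *Call made before allocation.* f = 0, and nothing is lost.

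**5. Spacing of counts.** With the same allowance at follow-up, the first two counts may be 3 − 2 = 1 to 5 − 0 = 5 months apart. This applies to both arms alike.

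**The case against.** The best counter-argument comes from the protocol itself. The Procedure section has the data collection instruments completed before the random numbers are checked, and the Data collection instruments section lists the pharmacy VAS and pill-count form among them. Read together, these place baseline adherence before allocation. That stands as evidence of intent, but it does not cancel the express permission for a later call. The sections conflict and need reconciling.

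Several limits also stand:

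- The 30-day look-back belongs to the VAS; the pill-count formula has no stated window. The contents of the Annex 5 pill-count form are not visible in the text reviewed, so the window cannot be settled from it.
- A prompt, constant effect is an assumption. The Hypotheses section expects drinking to keep falling over 12 months, and any effect of alcohol counselling on adherence is indirect, so a gradual build-up is plausible.
- Objective 5(b) does not name the pill count. Data Analysis names repeated-measures ANOVA only for the alcohol score and plans no adjustment for baseline pill count.
- The uneven spacing of counts adds noise, not a difference between arms.

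A reader might infer that the change score cancels the treatment effect outright, or even reverses it if an early effect fades. The documents support neither. Full cancellation is the limiting case f = 1, and no time course for adherence is given.

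**Conclusion.** The timing defect is real and limited in reach. As written, the first pill count can be a post-randomisation, post-intervention measurement. Comparing arms on change from it is then biased towards no difference whenever counselling has already moved adherence in the direction seen at follow-up. The loss can be anything from 0 to 100% of the effect. The 75% figure is an illustration that depends on call timing, look-back and speed of response.

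The point covers change in pill-count adherence and any use of that first count as an imputed value or covariate. It does not reach the comparison of observed levels at 3 and 12 months (Objective 4), which randomisation supports without a baseline. Nor does it reach the sample-size contrast, or change in VAS, provided the VAS is taken before allocation.

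**What to change.** Reconcile the Pill count, Procedure and Data collection instruments sections, and require the baseline pill count to be made before allocation. State likewise that the baseline VAS precedes allocation.

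If a pre-allocation call is not feasible:

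- label the first count as post-randomisation;
- do not use it for change scores, covariate adjustment or imputation;
- compare pill-count levels at 3 and 12 months between arms, adjusted for pre-allocation VAS in patients already on ART at baseline (others have no such value).

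The first option costs scheduling: the call must be fitted in before the random numbers are checked. The second costs only wording, but gives up a pill-count change score. Neither alters the sample size or the visit plan. Narrowing the window for follow-up calls would make spacing more even. It is optional, since unannounced calls need some latitude.
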